### Control Group

This study will have an active control group of SUD inpatients recruited from the same treatment facility as the patients in the intervention group. The control group will receive treatment as usual (TAU) for SUD patients. The treatment focuses on activities of daily living (ADL), including personal hygiene (e.g., washing oneself and brushing teeth); sleep hygiene, which focuses on regular sleep and wake-up times to help normalize sleep patterns; learning or relearning how to prepare and cook food; eating in a social setting at fixed times; house cleaning and work assignments relevant to making the ward run smoothly; structured socializing and group sessions, twice a day; and structured physical activity in the form of 30–120-min daily hikes and a longer weekly hike for a duration of 3–5 h.

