### Intervention Group

Participants in the intervention group will receive the same TAU as the control group, and they will also do four additional 30-min exercise protocols each week.

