### Randomization

Although we will not be conducting a true randomized control trial, the control and intervention groups will be run consecutively, and random assignment to these groups will occur naturally because the external allocation system of three separate units allocates patients with different needs to the SUD treatment waiting list independently of each other. Natural allocation will be aided further by SUD patients dropping out of the waiting list for entry to treatment.

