### Ethics Statement

This research project was approved by the Regional Ethics Committee for Medical Research Ethics, Western Norway (2011/1877). Written consent is collected from all participants.

All sensitive data (digital and non-digital) generated are confidential and will be treated according to the standards set by the Norwegian Data Inspectorate (Datatilsynet) and in compliance with the Health Research Act and the Personal Data Act.

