## Stepwise Procedures

Recruitment and eligibility. Patients will be recruited from the Helse Vest catchment area via the subacute treatment facility FAB. The Helse Vest catchment area consist of western Norway. FAB is mainly recruiting form the county of Rogaland and the main cities in the region Stavanger, Sandnes, and Haugesund. The patient target group for FAB is refered patients from the specialized health care system, with an addiction so serious that inpatient treatment is deemed necessary by a evaluation center. Comorbidity of light psychiatric diagnoses are accepted. We included patients of 18 years of age and upward. The patients often receive social benefits or disability pension. Education among the patient group is mixed from elementary school to university educated. We included patients mixed between first time rehabilitation to varying number of previous admission. Eligibility: SUD diagnosis, admitted as an inpatient to FAB; ≥18 years of age; passes the physical evaluation for the institution to perform intensive training; no medical history or illness that precludes participation in physical activity; and psychiatric diagnoses no more serious than the grading of light to moderate. Patients will be excluded from the study if their medical history (e.g., physical disability, disease, or injury) could interfere with or be exacerbated by physical activity. For example, patients with paralysis, severe pain, obstructive disease, glaucoma, or who are unable to sit, stand, and/or walk will be excluded, as well as patients with a severe cognitive deficit, such as dementia. A severe cognitive deficiency will be assessed based on the patients’ responses to two questions: “Do you have trouble with your memory that affects your daily life?” and “Have you been given a medical diagnosed of dementia?” Protocol deviations: If participants are absent from more than 60% of the training sessions. They are considered protocol violators. If they are not able to participate at allocated test times and complete the tests, they are considered protocol violators. They are still included in the study and tested as soon as possible. Statistical analyses will be performed both based on the principle of “intention to treat” including everyone regardless of protocol violation and “per protocol” analyses will be performed, comparing only those that have completed the protocol.

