1.Baseline testing. The physical and neuropsychological testing will be conducted within 2 weeks of admittance to the Salvation Army Treatment Center.2.The researchers will not conduct randomization, as there is natural allocation as a result of the SUD treatment allocation system, which will be continuous throughout the study.3.The control group is completed first. Structure is changed in the clinic and intervention group is started up after the last control patient has left the clinic.4.The intervention will consist of the physical exercise protocol, which will be conducted for 4 weeks.5.The final tests of physical function will be conducted the week after the exercise protocol is completed. The prospective follow-up will consist of cognitive testing carried out at 3, 6, 9, and 12 months after the baseline test.6.Discontinuation: Patients that don’t follow the protocol or don’t follow the TAU of the Facility will be discontinued. If they don’t complete the follow up test with in the allocated time line or neglect to perform the test they will be discontinued (Figure 1).

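### The arm is known whenever a patient is screened or consents, so entry can be selective by phase and the claim of naturally random assignment is wrong as written

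*Protocol article*

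**What the plan says.** Stepwise Procedures, item 3, fixes the order: "The control group is completed first. Structure is changed in the clinic and intervention group is started up after the last control patient has left". Item 2 adds: "The researchers will not conduct randomization, as there is natural allocation as a result of the SUD treatment allocation system".

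The Randomization section concedes that this is not a true randomised trial. It then says that random assignment to the groups will nonetheless arise naturally, because the "external allocation system of three separate units allocates patients with different needs to the SUD treatment waiting list independently of each other". It continues: "Natural allocation will be aided further by SUD patients dropping out of the waiting list for entry to treatment". The abstract likewise calls the sequential groups naturally randomised.

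On what each cohort receives, the Control Group section says "The control group will receive treatment as usual (TAU) for SUD patients", and this includes structured hikes. The Intervention Group section gives the same usual care and says "they will also do four additional 30-min exercise protocols each week".

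On entry, the Ethics Statement says "Written consent is collected from all participants". The eligibility text requires every participant to pass the institution's physical evaluation for intensive training, with no arm named. It also contains an exclusion that needs judgement about physical activity (the quote stops one word short): "Patients will be excluded from the study if their medical history (e.g., physical disability, disease, or injury) could interfere with or be exacerbated by physical".

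Limitations of the Study admits possible bias from unequal time periods and no other consequence of the sequence.

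**The concern.** Only one arm is open at any time, so the next assignment is never in doubt. Whoever applies the medical-history exclusion does so knowing whether the patient will train. A patient asked to consent in the second phase is presumably told about the exercise sessions, because consent to them must be informed. In the first phase a patient can presumably agree without facing that demand. Patients reluctant to train could then be more common among controls, even if the admissions themselves were identical in both phases.

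This differs from calendar-time confounding, which comes from changes in the clinic or the case mix. It also acts after the mechanisms that the Randomization section relies on. If willingness to train goes with recovery of cognition or quality of life, part of any difference between groups would reflect who entered and not what the programme did.

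**Working it through.** **1. Does the stated mechanism give random assignment?**

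- Independent referral decides who reaches the waiting list and when. It acts before screening and consent, so it cannot govern who is then judged eligible or agrees.
- Waiting-list dropout is patients removing themselves. That is self-selection and supplies no chance element. The documents do not show that it differs between phases, but it cannot aid random allocation.
- The calendar decides the arm, and staff know it in advance.

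The property claimed in the Randomization section is therefore absent.

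**2. Does anything else in the article close the gap?**

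- *Common eligibility criteria:* these screen ability to train, not willingness.
- *Intention-to-treat:* this starts from enrolled patients and cannot recover those who declined or were excluded before entry.
- *Limitations:* only time-period bias is named.

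**3. How large could it be?** The plan gives no figure for this, so there is none to reproduce. Its power statement (0.8 with 10 per group) does not enter the argument. Inputs from Anticipated Results are 30 per group, significance at 0.05, and 0.5 as the clinically relevant effect size (two-sided). The share declining and the outcome gap are assumptions.

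Spurious difference = (share unwilling among controls − share unwilling in the exercise cohort) × (outcome gap in SD between willing and unwilling patients).

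The table takes the extreme case in which no unwilling patient enters the exercise cohort, so the difference is share × gap. With no true effect, the rejection rate comes from a noncentral t with 58 df and noncentrality difference × √(30/2) = difference × 3.873.

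| Share declining | Gap (SD) | Spurious difference (SD) | Rejection | Share of 0.5 threshold |
|---|---|---|---|---|
| 10% | 0.3 | 0.03 | 5.1% | 6% |
| 10% | 0.8 | 0.08 | 6.1% | 16% |
| 20% | 0.5 | 0.10 | 6.7% | 20% |
| 30% | 0.5 | 0.15 | 8.8% | 30% |
| 40% | 0.3 | 0.12 | 7.4% | 24% |
| 40% | 0.8 | 0.32 | 23.0% | 64% |

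If some unwilling patients do enter the exercise cohort, the figures shrink. With 30% among controls, 15% in the exercise cohort and a gap of 0.5 SD, the difference is (0.30 − 0.15) × 0.5 = 0.075 SD, half the value in the table. If unwilling patients recovered better than willing ones, the sign would reverse.

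**The case against.** A reader might infer that the exercise cohort holds only patients willing to train, that controls accept nothing beyond usual care and testing, and that the bias therefore favours exercise. The documents do not support that much, for five reasons.

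- **Consent content is not visible.** The article says only that written consent is collected. Identical consent in both phases would fit every statement in it. Staff knowledge of the arm is certain from the sequence; patient knowledge is inferred.
- **Fitness is screened in both cohorts.** The requirement to be fit for intensive training names no arm. The fitness tests, including burpees and a one-mile walk, are not restricted to one arm either. A doubtful medical history therefore matters in the control phase too.
- **Usual care is already active.** Daily hikes of 30-120 minutes come to 7 × 0.5 = 3.5 h up to 7 × 2 = 14 h a week. With the weekly 3-5 h hike the total is 6.5-19 h, if that hike is additional. The programme adds 4 × 0.5 = 2 h. Its intensity differs, but patients averse to exertion have reason to decline in either phase.
- **Poor attenders stay in.** The plan foresees participants absent from more than 60% of sessions and keeps them in the intention-to-treat set, so the exercise cohort is not expected to be uniformly motivated.
- **The design is disclosed.** It is called quasi-experimental, and a reason for running the groups consecutively is given.

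These points limit what can be said about size and direction. They do not rescue the statement that assignment is random, and they do not supply a common condition of willingness at entry. An article may leave screening logs and consent wording to the full protocol, so their absence is not itself the error. The error is the positive claim about allocation.

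**Conclusion.** The point stands as a misstatement about allocation and an unacknowledged route for selection bias, not as a demonstrated bias. It is certain that the arm is known to staff at screening and consent, and that neither referral nor waiting-list dropout makes assignment random. It is probable, but inferred, that patients also know.

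Whether the two cohorts actually differ in willingness, by how much and in which direction, cannot be read from the documents. Under assumed refusal of 10-40% and an assumed outcome gap of 0.3-0.8 SD, the spurious difference runs from 0.03 SD, which is negligible, to 0.32 SD, which is not. Rejection with no true effect runs from 5.1% to 23%. These figures take the extreme case in which every unwilling patient is kept out of the exercise cohort, and they carry no evidence from this trial.

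**What to change.** 1. In the Randomization section, replace the claim of natural random assignment with a statement such as: *non-randomised, sequential cohorts; the arm is known at enrolment*. Delete the sentence that waiting-list dropout aids allocation. Change the matching description in the abstract.
2. Use the same eligibility form and the same consent in both phases, including stated willingness to take part in the exercise sessions if offered. This reduces the bias but does not remove it, because a control's answer is hypothetical.
3. Count eligible, excluded and declining patients by phase, with reasons, and report the two phases side by side.
4. Add selection at entry to Limitations of the Study, next to time-period bias.

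If controls are already enrolled, items 1 and 4 still apply, as do counts from whatever admission records exist. The cost is a wording change, one question at consent and a simple log. Control recruitment may be slightly slower, which the study can absorb because the limitations section says its length is not fixed and it can continue until the quota is met.

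### The protocol both keeps and discontinues patients who test late or miss a test, and applying the discontinuation rule to follow-up would stop collection of data the intention-to-treat analysis needs

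*Protocol article*

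**What the plan says.** Two rules stand close together under Stepwise Procedures.

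- **Protocol deviations paragraph.** It names two kinds of violator. One is defined by attendance ("If participants are absent from more than 60% of the training sessions"), the other by testing ("If they are not able to participate at allocated test times and complete the tests, they are considered protocol violators"). What happens to violators is then stated: "They are still included in the study and tested as soon as possible". The intention-to-treat analysis is described as "including everyone regardless of protocol violation", with a per-protocol analysis alongside it.
- **Item 6, Discontinuation.** The first sentence covers adherence and gives no threshold: "Patients that don’t follow the protocol or don’t follow the TAU of the Facility will be discontinued". The second covers testing: "If they don’t complete the follow up test with in the allocated time line or neglect to perform the test they will be discontinued".

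Item 5 of the same list puts the final physical tests in the week after the 4-week programme and the follow-up cognitive tests at 3, 6, 9 and 12 months after baseline. Under Intervention Group, patients receive the control group's usual treatment and "they will also do four additional 30-min exercise protocols each week". Anticipated Results plans a linear mixed model, described as accounting for missing data, where three or more measurements exist.

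**The concern.** A patient who arrives late for the 3-month test is kept and tested under one rule and discontinued under the other. If staff follow item 6, the 6-, 9- and 12-month scores of that patient are not collected, and no later analysis can restore them.

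The loss would probably not be random. The Introduction says that cognitive impairment contributes to dropout from treatment, and cognition is the outcome domain. Limitations of the Study acknowledges high dropout in earlier studies. The loss may also be somewhat greater in the intervention group, because only that group has training sessions to miss. The groups are sequential and not randomised, so selective loss would add to a comparability problem that already exists.

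**Working it through.** **Step 1. Compare the rules event by event.**

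| Event | Deviations paragraph | Item 6 | Compatible? |
|---|---|---|---|
| Late or missed follow-up test | Violator, kept, tested as soon as possible, in ITT | Discontinued | No |
| Poor training attendance | Violator above 60% absence, kept, in ITT | Discontinued, no threshold | Only if discontinuation means stopping treatment |
| Not following usual treatment | Not named; ITT covers everyone | Discontinued | Same condition |

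The attendance limit works out as 4 sessions × 4 weeks = 16 sessions; 0.6 × 16 = 9.6, so at least 10 missed sessions make a violator. Item 6 has no such limit.

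**Step 2. What can discontinued mean for a follow-up test?** Every test listed in item 5 falls after the 4-week programme has ended. Stopping the exercise programme is then no longer possible, so the natural reading is removal from follow-up.

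**Step 3. The plan's own figures.** The protocol gives no loss rate and no figure for this point. Its power statement (0.8 with at least 10 per group) rests on fitness and depression data without a stated effect size, so it cannot be reproduced. Nothing below uses it. The scale used is the 0.5 that Anticipated Results calls clinically relevant, with 30 per group and two-sided alpha 0.05.

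**Step 4. Illustration of bias.** Assumptions, none from the documents: no true effect; the least adherent fraction f is lost from the intervention group only; adherence correlates r with the outcome, and equally with the baseline score; baseline and follow-up correlate c.

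- Unadjusted shift = r × φ(z_f)/(1 − f). For f = 0.30: z = −0.524, φ(z) = 0.348, and 0.348/0.70 = 0.497. With r = 0.3 this gives 0.3 × 0.497 = 0.149 SD; with r = 0.5, 0.248 SD.
- Baseline-adjusted shift ≈ r × (1 − c) × φ(z_f)/(1 − f). Smallest case (r = 0.3, c = 0.8): 0.3 × 0.2 × 0.497 = 0.030 SD. Largest case (r = 0.5, c = 0.5): 0.5 × 0.5 × 0.497 = 0.124 SD. If the baseline slope is estimated in the selected data, the largest case is 0.13.

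**Step 5. Range over loss rates.** Power is for the two-sample t-test at d = 0.5; with no loss it is 0.48.

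| Loss f | Unadjusted shift, r = 0.3 / 0.5 | Adjusted shift, smallest to largest case | Power, intervention loss only | Power, both groups lose f |
|---|---|---|---|---|
| 10% | 0.058 / 0.097 | 0.012 to 0.049 | 0.46 | 0.44 |
| 20% | 0.105 / 0.175 | 0.021 to 0.087 | 0.43 | 0.40 |
| 30% | 0.149 / 0.248 | 0.030 to 0.124 | 0.41 (30 vs 21) | 0.35 (21 vs 21) |
| 40% | 0.193 / 0.322 | 0.039 to 0.161 | 0.38 | 0.31 |

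The bias columns belong with the one-group power column. The last column is a different scenario.

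**The case against.** The strongest defence is that the term is undefined and the analysis set is fixed explicitly. Item 6 refers to Figure 1, which is not available here and may clarify it. The sentence on protocol and usual treatment can mean stopping the programme or the stay, and that is compatible with analysing everyone. This stands for the first sentence of item 6 but not for the second, for the reason in Step 2.

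A reader might infer more than the text supports, in four ways:

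- **That the ITT set becomes a completer set.** It does not. Nothing in item 6 deletes collected data. A patient discontinued after a missed 6-month test still contributes baseline and 3-month scores to the mixed model.
- **That the plan creates missingness from unobserved outcomes, which a mixed model cannot repair.** The triggers are attendance, compliance and test timing, all of which are observed. The model handles loss explained by observed scores. It cannot fully correct the remainder, and as planned it does not cover the physical tests, which have two time points.
- **That only the intervention group loses patients.** The usual-treatment and test-timing rules bind both groups, and Control Group describes daily hikes of 30–120 min and a weekly hike of 3–5 h. Only the training-attendance route is confined to one group.
- **That the bias reaches half of the clinically relevant effect.** That is the unadjusted figure for one assumed case (0.248/0.5). The design has a pretest, and using it brings the same case to about a quarter (0.124/0.5).

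**Conclusion.** The contradiction is explicit for late or missed tests and needs no calculation. For non-adherence it exists only if discontinuation means leaving study follow-up. If item 6 is applied to follow-up, data needed for the promised intention-to-treat analysis will not be collected. That loss is plausibly related to cognition and somewhat more likely in the intervention group, though not confined to it.

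The direction and size of any bias are not established by the documents. At an assumed 30% selective loss in the intervention group only, with the correlations in Step 4, it is 0.15 to 0.25 SD unadjusted and about 0.03 to 0.12 SD after baseline adjustment. The power cost at d = 0.5 is 48% to 41%, or 35% if both groups lose 30%. The wording should be settled because it determines which data will exist.

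**What to change.** Reconcile the two places for data collection. Item 6 could state: *Non-adherence to the exercise protocol or to usual treatment, and a late or missed test, do not end study follow-up. All consenting patients are invited to every later scheduled test. Late tests are kept and recorded with their actual date.* In Anticipated Results, fit the intention-to-treat mixed model to everyone enrolled, using actual time since baseline, and keep the per-protocol analysis as the secondary comparison.

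State separately what discontinuation means for treatment, and whether the 60% absence limit applies to it. This point takes no position on that clinical rule.

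The cost is a wording change, continued invitations to tests that are already scheduled, and some timing noise from late tests.

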**FIGURE 1 F1:**
[figure not shown]
FAB, Stavanger 2019.

### Testing Procedures

#### Rockport 1-Mile Walk Test

This will be performed at the Stavanger outdoor stadium. Patients will be timed while walking 4 × 400 m, and pulse rate will be recorded with the final crossing of the finish line (George et al., 1998).

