## Abstract

This proposed study will examine whether structured physical activity reduces the recovery time of cognitive functioning during the early phase of substance use disorder treatment. Addiction or substance dependence is associated with neurobiological changes and cognitive impairment that can affect quality of life and the efficacy of therapy for up to a year after clinical detoxification. The biological, psychological, and social effects of physical exercise have the potential to be a therapeutic approach to increase quality of life and relieve symptoms associated with substance abuse, such as psychosis, depression, and anxiety. There is a dearth of research on physical activity and exercise in clinical substance use disorder patients. This protocol describes a clinical study that will examine cognitive recovery after substance abuse using physical exercise as a treatment intervention. We will use a quasi-experimental longitudinal clinical trial, with a pretest and multiple posttests, on naturally randomized sequential groups. Patients will be consecutively be recruited into the study groups, with a control group that is completed, before its followed by an intervention group, each with 30 patients. Patients will be enrolled 2 weeks after the start of detoxification, at which time all subjects will be inpatients at the Stavanger Salvation Army Treatment Center in the Norwegian specialized healthcare system. Cognition will be evaluated with a comprehensive battery of cognitive tests, including several tests of executive function. Physical fitness will be tested with the Rockport 1-Mile Walk Test, the 30-S Chair Stand Test, the 1-Min Burpee Test at baseline (within the first 2 weeks of admittance) and after 4 weeks. The intervention will be a 30-min workout at 70–90% of maximum heart rate (134–170 bpm), recorded and calculated by a Polar heart rate monitor. The intervention treatment will be administered four times a week for 4 weeks and will consist of high-intensity circuit training, high-intensity interval training, functional movement, and primitive reflex training. We anticipate improvement in both the control and intervention groups, with the exercise intervention group having the greatest increase in recovery of cognitive function because of the combination of functional full body movements and primitive movement training in an intense interval training program.

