## Anticipated Results

In this study, we expect the participants in both the control and intervention groups to show progress in physical and mental health after a period of substance abuse. We believe that the data generated in this project will mostly be at the interval or ratio level (whether the rating of perceived exertion is ordinal or interval data will not be discussed here). We will use the mean as a measure of central tendency for the group results for the neurocognitive test, while the reflexes we use frequency and proportions, and the standard deviation to express the spread of results within the group. If useful, the standard error of the mean (SEM) will be used to express the accuracy of the mean value. If the results are highly skewed (skewness > 1.5), we will use a log transformation and geometric mean together with a 95% confidence interval to express central and spread tendencies. To compare results over time from pretest to posttests, and between-group differences, we will use repeated measures ANOVA/*t*-tests with Sidak/Holm *post hoc* tests, where we have collected three or more measurements a linear mixed modeling accounting for the missing data will be used. Group comparisons will be made with an ANOVA/*t*-test for independent groups. If the test of normality should fail (Kolmogorov–Smirnov with Lilliefors correction), the corresponding non-parametric tests will be used, i.e., the Wilcoxon–Mann–Whitney rank sum test for independent *t*-tests and repeated measures ANOVA for ranks (Tukey’s *post hoc* test). Statistical significance will be set at a *p*-value of ≤0.05, and effect sizes will be calculated according to Cohen (1988), with the help of an online effect size calculator (the CEM effect size calculator, Center for Evaluation and Monitoring, Durham University, United Kingdom^1^). An effect size of ≥0.5 will be considered clinically relevant (two-sided). If there is a need for building indexes of different types of scores, *Z*-scores will be used. Based on previously published data on fitness development and depression scores, we should be able to attain statistical power of 0.8 with at least 10 subjects in each of the two groups. Nevertheless, we have set target recruitment at *n* = 30 for each group.

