### Limitations of the Study

Because the intervention and control groups will be run consecutively rather than concurrently, there is the potential for non-equivalent time periods to create bias. However, we chose this approach because previous studies had suffered recruitment failures and high dropout rates. The length of the proposed study is not fixed, and because of our funding and support, this study can continue until the quota for participants is met.

This study is designed to accommodate clinical realities. Thus, different SUD groups are not fractionated during treatment, and the project protocol does not divide different groups of SUD after clinical classification. This may create some problems with the results from baseline because of various issues with the abuse of different drugs and possible side effects that might affect the test results differently. We will account for this Statistically.

Finally, the patient population will be recruited straight out of a detoxification clinic, which will most likely influence the test results. However, this may actually be an advantage, because having access to patients so quickly after controlled, medically supervised detoxification may give us a more accurate picture of their mental status when the patients are at their lowest point in their recovery trajectories.

The Norwegian Ministry of Health and Social Affairs and the Salvation Army of Norway have provided financial support for this study.

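### The outdoor walk test in two non-overlapping cohorts lets a difference in how weather drifts between visits pass for, or hide, a fitness effect; the size is unknown

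*Protocol article*

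**What the plan says.** The Abstract lists the fitness tests and their timing: "Physical fitness will be tested with the Rockport 1-Mile Walk Test, the 30-S Chair Stand Test, the 1-Min Burpee Test at baseline", and again after 4 weeks. The Rockport section fixes the place, "This will be performed at the Stavanger outdoor stadium", and the measurements: "Patients will be timed while walking 4 × 400 m, and pulse rate will be recorded with the final crossing of the finish line". By contrast, the chair stand section places that test at the treatment center.

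Stepwise Procedures sets the dates. For baseline, "The physical and neuropsychological testing will be conducted within 2 weeks of admittance to the Salvation Army Treatment Center". For the last measurement, "The final tests of physical function will be conducted the week after the exercise protocol is completed". It also sets the order of the groups: the control group is completed, and the "intervention group is started up after the last control patient has left the clinic".

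Anticipated Results gives the analysis. Pretest and posttests are compared by repeated measures ANOVA or t-tests, and a mixed model is reserved for outcomes measured three or more times. "Group comparisons will be made with an ANOVA/*t*-test for independent groups". Rank tests are the fallback. No calendar or test-condition term is named.

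Limitations of the Study concedes in general that consecutive groups may bring bias from non-equivalent periods. It does not mention the outdoor test and attaches no remedy. The statistical adjustment promised there concerns different drugs of abuse, not calendar period. The same section says "The length of the proposed study is not fixed".

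**The concern.** Walk time and finish pulse can both respond to temperature, wind and the state of the track. When groups are recruited side by side, such effects fall on both alike and cost only precision. Here calendar time and group are tied together, so nothing in the design balances outdoor conditions.

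A baseline walk might seem to deal with this. It does so only for a seasonal level shared by a patient's two visits. What remains is the change in conditions between the visits. If one cohort is tested mostly while conditions improve and the other mostly while they worsen, the difference between those drifts lands in the between-group difference in change. It could then be reported as a fitness effect of the programme, or could cancel a real one.

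**Working it through.** **Inputs from the article.** Outdoor walk; two visits; cohorts with no calendar overlap; target of 30 per group; significance at p ≤ 0.05; an effect size of 0.5 treated as clinically relevant. The article gives no figure for weather or season, so there is nothing of its own to reproduce on this point.

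**Gap between visits.** If baseline falls just before the programme and the final test right after it, the gap is 0 + 4 = 4 weeks. If baseline falls at admittance, the programme starts two weeks later (an assumption) and the final test comes at the end of the following week, the gap is 2 + 4 + 1 = 7 weeks. I use 5 weeks as the central value.

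**What the planned test estimates.** With two visits, the group-by-time test in a repeated measures ANOVA is the t-test on change. Write each cohort's mean change as true change plus mean drift in conditions:

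difference in change = true effect + (drift in intervention cohort − drift in control cohort).

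The bracket is the bias.

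**How large the bracket can be.** Assume a yearly sine wave of amplitude A in the walk score, period P = 52.18 weeks, gap g, and even recruitment over a window of L weeks per cohort. The largest possible difference in drift is

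4A · sin(πg/P) · [sin(πL/P) / (πL/P)].

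If the second cohort starts g weeks after the first cohort's recruitment window closes, multiply by |sin(π(L + g)/P)|. For g = 5, sin(πg/P) = 0.2965. For L = 13 the window factor is 0.901, so the maximum is 4 × 0.2965 × 0.901 = 1.07A. Back to back it is 1.07A × 0.884 = 0.94A.

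| Window per cohort | Maximum, any spacing | Maximum, back to back |
|---|---|---|
| 3 months | 1.07A | 0.94A |
| 6 months | 0.76A | 0.72A |
| 9 months | 0.36A | 0.17A |
| 12 months | 0 | 0 |

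For 3-month windows back to back, the figure is 0.73A with a 4-week gap and 1.38A with a 7-week gap. These are worst cases over starting date; an actual start date can give less.

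**Consequence for the test.** Let b be the bias in SDs of the change, with no true effect. The t-statistic has 58 degrees of freedom and noncentrality b·√(30/2) = 3.873b.

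| b | Noncentrality | Two-sided type I error |
|---|---|---|
| 0 | 0 | 5% |
| 0.1 | 0.39 | 7% |
| 0.2 | 0.77 | 12% |
| 0.3 | 1.16 | 21% |
| 0.5 | 1.94 | 48% |

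**Linking the two tables.** With A in SDs of the change, back-to-back 3-month windows and a 5-week gap, the worst case reaches b = 0.1 at A = 0.1/0.94 = 0.11 and b = 0.5 at A = 0.5/0.94 = 0.53. With 6-month windows these become 0.14 and 0.69. The article does not say where A lies.

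**The case against.** The strongest reply is that the size rests wholly on assumption. The article gives neither the cohorts' calendar windows nor any weather effect. Study length is open and earlier studies are said to have had recruitment failures, so long windows are plausible, and the bias then shrinks towards zero. This stands, and it rules out stating as fact that the change score measures season.

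Second, a reader might infer that patients walk in whatever weather occurs, all year and on ice. The article does not say so. Its description of the test is two sentences long, and rules for postponing a test may sit in the full protocol, which is not shown. Their absence is not counted here.

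Third, a reader might take the walk as the test that must carry the fitness conclusion, because the burpee is itself trained and air squats resemble the chair stand. The documents do not support this. Walking is the cooldown, both groups hike under usual treatment, the article also links burpees to aerobic performance, and no section gives the walk that role. Cognition is the main question.

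Fourth, the Limitations section already admits period bias. That is fair, but the admission is general. It does not identify this route into a specific measurement, and it leads to no recording or adjustment.

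Finally, 4 × 400 m is 1,600 m against a mile of 1,609.3 m, or 9.3 m short. This is equal in both groups and the article states no 1-mile equation, so it does not bear on the comparison.

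**Conclusion.** The mechanism holds on what the article states: an outdoor timed walk with finish pulse, no calendar overlap between groups, and an analysis with no term for conditions. A difference between cohorts in how conditions drift between visits cannot be told apart from a fitness effect. It is a risk of unknown size, not a demonstrated bias.

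The range of 7% to 48% for the type I error holds only if the spurious shift is 0.1 to 0.5 SD of the change with 30 per group. The upper end coincides with the article's own threshold for clinical relevance. Larger error rates can be produced: an assumed net shift of 2% to 4% on a 15-minute walk with an SD of change of 0.8 to 1.0 min gives 21% to 81%. None of those inputs is in the article, and the range leaves out small shifts, so it should not be read as an estimate.

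The point limits what can be concluded from one of three supporting fitness tests. It leaves the cognitive outcome untouched.

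**What to change.** 1. **Rockport 1-Mile Walk Test:** record the test date, temperature and wind or track condition at every walk.
2. **Anticipated Results:** analyse walk time and finish pulse by ANCOVA with the baseline value. This alone does not remove the drift, so add a sensitivity model with one or two condition terms named in advance, for example the change in temperature between visits. Keep to that number; separate terms for temperature, wind and surface at both visits would be too many for 60 patients.
3. **Limitations of the Study:** say that the admitted period bias applies in particular to the outdoor walk, and read its result accordingly.

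The cost is a few fields on the test form and one extra model. Where conditions are correlated with group, the adjusted comparison loses precision, and if the cohorts' conditions hardly overlap it rests on extrapolation. That is why it belongs in a sensitivity analysis. Site-level details such as track state would be hard to reconstruct later, so recording has to start with the testing.
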